### Study treatments

Both the group CBT and MBSR class series consist of eight weekly 2-hour sessions supplemented by home activities.

#### Mindfulness-based stress reduction

Mindfulness-based stress reduction, a 30-year-old treatment program developed by Jon Kabat-Zinn, is well-described in the literature [32-34]. The authors of a recent meta-analysis found that MBSR had moderate effect sizes for improving the physical and mental well-being of patients with a variety of health conditions [16]. Our MBSR program is closely modeled on the original one and includes eight weekly 2-hour classes (summarized in Table 3), a 6-hour retreat between weeks 6 and 7 and up to 45 minutes per day of home practice. Our MBSR protocol was adapted by a senior MBSR instructor from the 2009 MBSR instructor’s manual used at the University of Massachusetts [35]. This manual permits latitude in how instructors introduce mindfulness and its practice to participants. The handouts and home practice materials are standardized for this study.

**Table 3 T3:** **Content of cognitive-behavioral therapy and mindfulness-based stress reduction class sessions**^
**a**
^

**Session**	**CBT**	**MBSR**
1	Rationale and evidence base for CBT, pain neurobiology, overview of skills, rationale for relaxation training, diaphragmatic breathing instruction, introduction to behavioral goal setting (physical activity and home practice)	Setting expectations, defining mindfulness, engaging in mindfulness exercise and movement, abdominal breathing instructions, introducing home practice
2	Behavioral goal setting, physical activity and pacing activity, pleasant event scheduling, pain flare-up plan, diaphragmatic breathing and seven-muscle-group progressive muscle relaxation (PMR) instruction	Perception and responding creatively to perceptions, engaging in yoga, body scan, discussion of developing a practice
3	Role of thoughts and feelings in pain, introduction to the CBT model, thought-monitoring record, diaphragmatic and four-muscle-group PMR instruction, setting and working toward behavioral goals	Pleasure and power of being present, engaging in yoga, walking meditation, discussing how to bring more pleasant events into our lives
4	Challenging automatic thoughts related to pain, setting and working toward behavioral goals, diaphragmatic breathing and four-muscle-group/no-tension PMR instruction	Getting unstuck from old patterns, engaging in yoga and/or movement, sitting meditation, stress (define and identify how and why we stay stuck), dealing with pain
5	Challenging automatic thoughts and generating alternate thoughts, distraction techniques, brief body scan relaxation instruction, setting and working toward behavioral goals	Reacting and responding differently to stress, engaging in yoga, participating in guided meditation, establishing coping strategies (living with difficulties)
6	Alternate thoughts, thought stopping, behavioral activation, mini-relaxation instruction, setting and working toward behavioral goals	Learning about communication patterns, engaging in yoga and/or meditation, styles of communicating with others (effective and ineffective)
7	Rehearsing pain coping skills, identifying and challenging negative thoughts, setting and working toward behavioral goals, mini-relaxation instruction, sleep tips	Integrating learning from techniques, yoga and/or meditation, practical ways to bring mindfulness into daily life
8	Maintenance of coping skills, relapse prevention, personal plan for the future	This is the rest of your life, review mindfulness techniques and applications, closure

^a^CBT, Cognitive-behavioral therapy; MBSR, Mindfulness-based stress reduction.

Participants will be given a packet of information during the first class that includes a course outline and instructor contact information; information about mindfulness, meditation, communication skills and effects of stress on the body, emotions and behavior; homework assignments; poems; and a bibliography. All sessions will include mindfulness exercises, and all but the first will include yoga or other forms of mindful movement. Participants will be given audio recordings of the mindfulness and yoga techniques, which will have been recorded by their own instructors. Participants will be asked to practice the techniques discussed in each class daily for up to 45 minutes throughout the intervention period and after classes end. They will also be assigned readings to complete before each class. Time will be devoted in each class to a review of challenges that participants have had in practicing what they learned in previous classes and with their homework. An optional day of practice on the Saturday between the sixth and seventh classes will be offered. This 6-hour “retreat” will be held with the participants in silence and only the instructor speaking. This will provide participants an opportunity to deepen what they have learned in class.

#### Cognitive-behavioral therapy

CBT for chronic pain is well-described in the literature and has been found to be modestly to moderately effective in improving chronic pain problems [9-13]. There is no single, standardized CBT intervention for chronic pain, although all CBT interventions are based on the assumption that both cognition and behavior influence adaptation to chronic pain and that maladaptive cognition and behavior can be identified and changed to improve patient functioning [36]. CBT emphasizes active, structured techniques to teach patients how to identify, monitor and change maladaptive thoughts, feelings and behaviors, with a focus on helping patients to acquire skills that they can apply to a variety of problems and collaboration between the patient and therapist. A variety of techniques are taught, including training in pain coping skills (for example, use of positive coping self-statements, distraction, relaxation and problem-solving). CBT also promotes setting and working toward behavioral goals.

Both individual and group formats have been used in CBT. Group CBT is often an important component of multidisciplinary pain treatment programs. We will use a group CBT format because it has been found to be efficacious [37-40], is more resource-efficient than individual therapy and provides patients with the potential benefits deriving from contact with, and support and encouragement from, others with similar experiences and problems. In addition, using group formats for both MBSR and CBT will eliminate intervention format as a possible explanation for any differences observed between the two therapies.

For this study, we developed a detailed therapist’s manual with content specific for each session, as well as a participant’s workbook containing materials for use in each session. We developed the therapist’s manual and participant’s workbooks based on existing published resources as well as on materials we have used in prior studies [39-47].

The CBT intervention (Table 3) will consist of eight weekly 2-hour sessions that will provide (1) education about the role of maladaptive automatic thoughts (for example, catastrophizing) and beliefs (for example, one’s ability to control pain, hurt equals harm) common in people with depression, anxiety and/or chronic pain and (2) instruction and practice in identifying and challenging negative thoughts, the use of thought-stopping techniques, the use of positive coping self-statements and goal-setting, relaxation techniques and coping with pain flare-ups. The intervention will also include education about activity pacing and scheduling and about relapse prevention and maintenance of gains. Participants will be given audio recordings of relaxation and imagery exercises and asked to set goals regarding their relaxation practice. During each session, participants will complete a personal action plan for activities to be completed between sessions. These plans will be used as logs for setting specific home practice goals and checking off activities completed during the week to be reviewed at the next week’s session.

#### Usual care

The usual care group will receive whatever medical care they would normally receive during the study period. To minimize possible disappointment with not being randomized to a mind–body treatment, participants in this group will receive $50 compensation.

### Class sites

The CBT and MBSR classes will be held in facilities close to concentrations of GHC members in Washington state (Bellevue, Bellingham, Olympia, Seattle, Spokane and Tacoma).

### Instructors

All MBSR instructors will have received either formal training in teaching MBSR from the Center for Mindfulness at the University of Massachusetts or equivalent training. They will themselves be practitioners of both mindfulness and a body-oriented discipline (for example, yoga), will have taught MBSR previously and will have made mindfulness a core component of their lives. The CBT intervention will be conducted by doctorate-level clinical psychologists with previous experience in providing CBT to patients with chronic pain.

### Training and monitoring of instructors

All CBT instructors will be trained in the study protocol for the CBT intervention by the study’s clinical psychologist investigators ([name] and [name]), who are very experienced in administering CBT to patients with chronic pain. [name] will supervise the CBT instructors. One of the investigators ([name]) will train the MBSR instructors in the adapted MBSR protocol and supervise them. Each instructor will attend weekly supervision sessions, which will include discussion of positive experiences, adverse events, concerns raised by the instructor or participants and protocol fidelity. Treatment fidelity checklists highlighting the essential components for each session were created for both the CBT and MBSR arms. A trained research specialist will use the fidelity checklist during live observation of every session. The research specialist will provide feedback to the supervisor to facilitate weekly supervision of the instructors. In addition, all sessions will be audio-recorded. The supervisors will listen to a random sample and requested portions of sessions and will monitor them using the fidelity checklist. Feedback will be provided to the instructors during their weekly supervision sessions. Treatment fidelity will be monitored in both intervention groups by [name] and [name] with assistance from research specialists. In addition, they will review and rate on the fidelity checklist a random sample of the recorded sessions.

### Participant retention and adherence to home practice

Participants will receive a reminder call before the first class and whenever they miss a class. They will be asked to record their daily home practice on weekly logs. Questions about their home practice during the prior week will also be included in all follow-up interviews. To maintain interviewer blinding, adherence questions will be asked after all outcome data have been recorded.

### Measures

We will assess a variety of participant baseline characteristics, including sociodemographic characteristics, back pain history and expectations of the helpfulness of the mind–body treatments for back pain (Table 4).

**Table 4 T4:** **Baseline and follow-up measures**^
**a**
^

**Measures**	**Baseline**	**4 wk**	**8 wk**	**26 wk**	**52 wk**
Baseline characteristics					
Patient characteristics (age, sex, education, race, ethnicity, marital status, income, work status, number of pain sites)	x				
Back pain (pain duration, interference with activities, days of pain in previous 6 months, previous spinal injections, whether pain radiates into leg below knee)	x				
Expectations for back pain improvement in general and as result of MBSR or CBT	x				
Primary outcomes					
Back pain-related activity limitations in past week (modified RDQ)	x	x	x	x	x
Bothersomeness of back pain in past week (0 to 10 scale)	x	x	x	x	x
Secondary outcomes					
Characteristic pain intensity (GCPS) (average of pain now, worst pain, average pain)	x		x	x	x
Depression (PHQ-8)	x		x	x	x
Anxiety (GAD-2)	x		x	x	x
Medications used for back pain in past week	x		x	x	x
Exercise in past week (back pain–specific and general)	x		x	x	x
Global improvement (PGIC)			x	x	x
Program’s impact on thoughts, feelings, reactions, activities (open-ended)			x	x	x
Potential mediators					
MBSR: mindfulness (FFMQ-SF), pain acceptance (CPAQ-8)	x	x	x	x	x
CBT: pain beliefs and appraisals (PSEQ; SOPA 2-item control, disability and harm scales; PCS), pain coping strategies (CPCI activity pacing scale and 2-item relaxation scale)	x	x	x	x	x
Cost-effectiveness outcomes					
Quality of life (EQ-5D, SF-6D from the SF-12)	x	x	x	x	x
Out-of-plan visits paid for by patients since previous follow-up interview	x		x	x	x
Absenteeism, presenteeism (WPAI-CLBP)	x		x	x	x
Costs paid by GHC (payer) for back-related utilization of services (visits, tests, prescriptions) and total costs (GHC members only) (from GHC electronic medical records for year prior to trial and for follow-up year)					
Intervention-related information					
Class attendance (class records)					
Adverse experiences from classes or home practice		x	x	x	x
New serious health problems since entering study		x	x	x	x
Self-reported home practice		x	x	x	x
Perceived helpfulness of classes and home practice			x	x	x
Would recommend program to friends			x	x	x

^a^CBT, Cognitive-behavioral therapy; CPAQ-8, 8-item Chronic Pain Acceptance Questionnaire; CPCI, Chronic Pain Coping Inventory; EQ-5D, European Quality of Life (EuroQol) instrument in 5 dimensions; FFMQ, Five Facet Mindfulness Questionnaire; GAD-2, 2-item Generalized Anxiety Disorder scale; GCPS, Graded Chronic Pain Scale; MBSR, Mindfulness-based stress reduction; PCS, Pain Catastrophizing Scale; PGIC, Patient Global Impression of Change scale; PHQ-8,8 item Patient Health Questionnaire; PSEQ, Patient Self-efficacy Questionnaire; RDQ, Roland Disability Questionnaire; SF-6D, Short Form Health Survey in 6 dimensions; SF-12, 12-item Short Form Health Survey; SOPA, Survey of Pain Attitudes; WPAI-CLBP, Work Productivity and Activity Impairment Questionnaire–Chronic Low Back Pain.

We will assess a core set of outcomes for patients with spinal disorders (back-related function, pain, general health status, work disability and patient satisfaction) [48] that are consistent with the Initiative on Methods, Measurement, and Pain Assessment in Clinical Trials recommendations for clinical trials of chronic pain treatment efficacy and effectiveness [49]. We will measure both short-term outcomes (8 and 26 weeks) and long-term outcomes (52 weeks). We will also include a brief, 4-week, midtreatment assessment to permit analyses of the hypothesized mediators of the effects of MBSR and CBT on the primary outcomes. The primary study endpoint is 26 weeks. Participants will be paid $20 for each follow-up interview completed to maximize response rates.

#### Co–primary outcome measures

The co–primary outcome measures will be back-related activity limitations and back pain bothersomeness.

Back-related activity limitations will be measured with the modified RDQ, which asks whether 23 specific activities have been limited due to back pain (yes or no) [30]. We have further modified the RDQ to ask a question about the previous week rather than just “today”. The original RDQ has been found to be reliable, valid and sensitive to clinical changes [31,48,50-53], and it is appropriate for telephone administration and use with patients with moderate activity limitations [50].

Back pain bothersomeness will be measured by asking participants to rate how bothersome their back pain has been during the previous week on a 0 to 10 scale (0 = “not at all bothersome” and 10 = “extremely bothersome”). On the basis of data compiled from a similar group of GHC members with back pain, we found this bothersomeness measure to be highly correlated with a 0 to 10 measure of pain intensity (*r* = 0.8 to 0.9; unpublished data ([name] and [name]) and with measures of function and other outcome measures [54]. The validity of numerical rating scales of pain has been well-documented, and such scales have demonstrated sensitivity in detecting changes in pain after treatment [55].

We will analyze and report these co–primary outcomes in two ways. First, for our primary endpoint analyses, we will compare the percentages of participants in the three treatment groups who achieve clinically meaningful improvement (≥30% improvement from baseline) [56,57] at each time point (with 26-week follow-up being the primary endpoint). We will then examine, in a secondary outcome analysis, the adjusted mean differences between groups on these measures at the time of follow-up.

#### Secondary outcome measures

The secondary outcomes that we will measure are depressive symptoms, anxiety, pain-related activity interference, global improvement with treatment, use of medications for back pain, general health status and qualitative outcomes.

Depressive symptoms will be assessed with the Patient Health Questionnaire-8 (PHQ-8) [58]. With the exception of the elimination of a question about suicidal ideation, the PHQ-8 is identical to the PHQ-9, which has been found to be reliable, valid and responsive to change [59,60].

Anxiety will be measured with the 2-item Generalized Anxiety Disorder scale (GAD-2), which has demonstrated high sensitivity and specificity in detecting generalized anxiety disorder in primary care populations [61,62].

Pain-related activity interference with daily activities will be assessed using three items from the Graded Chronic Pain Scale (GCPS). The GCPS has been validated and shown to have good psychometric properties in a large population survey and in large samples of primary care patients with pain [63,64]. Participants will be asked to rate the following three items on a 0 to 10 scale: their current back pain (back pain “right now”), their worst back pain in the previous month and their average pain level over the previous month.

Global improvement with treatment will be measured with the Patient Global Impression of Change scale [65]. This single question asks participants to rate their improvement with treatment on a 7-point scale that ranges from “very much improved” to “very much worse,” with “no change” used as the midpoint. Global ratings of improvement with treatment provide a measure of overall clinical benefit from treatment and are considered one of the core outcome domains in pain clinical trials [49].

Use of medications and exercise for back pain during the previous week will be assessed with the 8-, 26- and 52-week questionnaires.

General health status will be assessed with the 12-item Short Form Health Survey (SF-12) [66], a widely used instrument that yields summary scores for physical and mental health status. The SF-12 will also be used to calculate quality-adjusted life-years (QALYs) using the Short Form Health Survey in 6 dimensions in the cost-effectiveness analyses [67].

Qualitative outcomes will be measured with open-ended questions. We have included open-ended questions in our previous trials and found that they yield valuable insights into participants’ feelings about the value of specific components of the interventions and the impact of the interventions on their lives. We therefore will include open-ended questions about these issues at the end of the 8-, 26- and 52-week follow-up interviews.

#### Measures used in mediator analyses

In the MBSR arm, we will evaluate the mediating effects of increased mindfulness (measured with the Nonreactivity, Observing, Acting with Awareness, and Nonjudging subscales of the Five Facet Mindfulness Questionnaire short form [68-70]) and increased pain acceptance (measured with the Chronic Pain Acceptance Questionnaire [71,72]) on the primary outcomes. In the CBT arm, we will evaluate the mediating effects of improvements in pain beliefs and/or appraisals (measured with the Patient Self-Efficacy Questionnaire [73]; the Survey of Pain Attitudes 2-item Control, Disability, and Harm scales [74-76]; and the Pain Catastrophizing Scale [77-80]) and changes in the use of pain coping strategies (measured with the Chronic Pain Coping Inventory 2-item Relaxation scale and the complete Activity Pacing scale [81,82]) on the primary outcomes. Although we expect the effects of MBSR and CBT on outcomes to be mediated by different variables, we will explore the effects of all potential mediators on outcomes in both treatment groups.

#### Measures used in the cost-effectiveness analyses

Direct costs will be estimated using cost data extracted from the electronic medical records for back-related services provided or paid by GHC and from patient reports of care not covered by GHC. Indirect costs will be estimated using the Work Productivity and Activity Impairment questionnaire [83]. The effectiveness of the intervention will be derived from the SF-12 general health status measure [84].

### Data collection, quality control and confidentiality

Data will be collected from participants by trained telephone interviewers using a computer-assisted telephone interview (CATI) version of the questionnaires to minimize errors and missing data. Questions about experiences with specific aspects of the interventions (for example, yoga, meditation, instruction in coping strategies) that would unmask interviewers to treatment groups will be asked at each time point after all other outcomes have been assessed. We will attempt to obtain outcome data from all participants in the trial, including those who never attend or drop out of the classes, those who discontinue enrollment in the health plan and those who move away. Participants who do not respond to repeated attempts to obtain follow-up data by telephone will be mailed a questionnaire including only the two primary outcome measures and offered $10 for responding.

We are will collect information at every stage of recruitment, randomization and treatment so that we can report patient flow according to the CONSORT (Consolidated Standards of Reporting Trials) guidelines [85]. To maintain the confidentiality of patient-related information in the database, unique participant study numbers will be used to identify patient outcomes and treatment data. Study procedures are in place to ensure that all masked personnel will remain masked to treatment group.

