#### Adverse experiences

We will collect data on adverse experiences (AEs) from several sources: (1) reports from the CBT and MBSR instructors of any participants’ experiences of concern to them; (2) the 8-, 26- and 52-week CATI follow-up interviews in which the participants are asked about any harm they felt during the CBT or MBSR treatment and any serious health problems they had had during the respective time periods; and (3) spontaneous reports from participants. The project coinvestigators and a GHC primary care internist will review AE reports from all sources weekly. Any serious AEs will be reported promptly to the GHC IRB and the DSMB. AEs that are not serious will be recorded and included in regular DSMB reports. Any identified deaths of participants will be reported to the DSMB chair within 7 days of discovery, regardless of attribution.

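### The mailed fallback form holds only the two primary outcomes, so mail-only responders count for efficacy but are not asked about harms or serious health problems at that time point

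*Protocol article*

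**What the plan says.** Follow-up is by computer-assisted telephone interview. Data collection, quality control and confidentiality describes a fallback for people whom the callers repeatedly fail to reach: they "will be mailed a questionnaire including only the two primary outcome measures and offered $10 for responding". The two measures are the modified RDQ and the bothersomeness rating.

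The Adverse experiences section names three sources of safety data:

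- "reports from the CBT and MBSR instructors of any participants’ experiences of concern to them"
- "the 8-, 26- and 52-week CATI follow-up interviews in which the participants are asked about any harm they felt during the CBT or MBSR treatment", together with "any serious health problems they had had during the respective time periods"
- "spontaneous reports from participants"

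Training and monitoring of instructors adds weekly supervision sessions, "which will include discussion of positive experiences, adverse events, concerns raised by the instructor or participants and protocol fidelity". Table 4 schedules adverse experiences and the item "New serious health problems since entering study" at 4, 8, 26 and 52 weeks. The Adverse experiences section mentions only the 8-, 26- and 52-week interviews.

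Under Primary analyses, if follow-up reaches the expected 89%, the primary analysis is a complete case analysis of whatever follow-up outcomes were observed. A mailed RDQ or bothersomeness answer would be part of it.

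**The concern.** Of the three safety sources, only the interview puts a question to participants in all three arms. Instructor reports require an instructor, so usual care has none, and they are tied to classes that last 8 weeks of a 52-week follow-up. Spontaneous reports depend on the participant taking the initiative. When the mailed form replaces a call, the one source common to all arms drops out for that person at that visit, although the trial has reached them and receives their efficacy answers.

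Two things are at stake. First, solicited safety data will cover fewer people than the primary outcomes, and a reader could take the event counts to cover everyone with outcome data. Second, the Stopping rules section makes an unacceptable risk of serious adverse events in one or more arms the only ground for stopping. That judgement is easier when ascertainment is as complete and as similar across arms as it can cheaply be made.

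**Working it through.** **1. The plan's own figures.** The target is 264 evaluable participants (88 per group) with 11% loss to follow-up (Sample size and detectable differences).

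- 264 / (1 − 0.11) = 296.6, rounded up to 297
- 88 / (1 − 0.11) = 98.9, rounded up to 99 per group

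Both match the article. (The abstract gives 397, but 3 × 99 = 297, and 297 is used here.) The number expected to be followed up is 297 × 0.89 = 264.3, or about 88 per arm.

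**2. What a mail-only responder supplies at one visit.**

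| Item | Telephone interview | Mailed form |
|---|---|---|
| Modified RDQ, bothersomeness | yes | yes |
| Counted in the primary analysis | yes | yes |
| Harm from classes or home practice | asked | not asked |
| New serious health problems | asked | not asked |

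**3. What the other sources can recover.**

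- *Instructor reports and weekly supervision.* These are possible in the class arms while classes run. They are weak for someone who has stopped attending and do not exist for usual care.
- *Spontaneous reports.* Possible in any arm, but nobody asks.
- *Another completed interview.* Table 4 words the serious-problem item as cumulative from study entry, so a later call could recover a missed event. The Adverse experiences section ties the question to the period each interview covers, so recovery is not assured. After week 52 there is no later interview.
- *Deaths.* Any identified death goes to the DSMB chair. This does not help with non-fatal events.

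**4. Size of the gap.** Let N = 297 randomized, f = 0.89 followed up (taken to include mailed replies) and m = the share of those followed up who answer by mail. The article does not give m; 0 to 0.15 is an assumed range.

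- People with outcomes but no solicited safety data at that visit: N × f × m
- Solicited safety coverage of those randomized: f × (1 − m)

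| m (assumed) | People, all arms | People per arm (99 × 0.89 × m) | Solicited safety coverage | Outcome coverage |
|---|---|---|---|---|
| 0% | 0 | 0 | 89% | 89% |
| 2% | 5.3 | 1.8 | 87% | 89% |
| 5% | 13.2 | 4.4 | 85% | 89% |
| 10% | 26.4 | 8.8 | 80% | 89% |
| 15% | 39.6 | 13.2 | 76% | 89% |

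The per-arm column assumes that mail replies are spread evenly across arms. The article does not say whether they are.

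**The case against.** The strongest reply is that the mailed form takes no safety data away. Without it, someone who does not answer the telephone would give neither outcomes nor interview safety data. The gap comes from telephone non-response, and a very short form is a sensible way to protect return of the co-primary outcomes. The article also does not say that adverse events will be reported over the efficacy denominator; that detail could sit in an analysis plan that is not shown. Participants who miss a class get a reminder call, so class drop-outs are not simply out of contact, although the article does not say that these calls ask about harm.

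Most of this is fair. The form does not create the non-response, and nothing in the plan is contradictory here. What remains is that contact has been made and the safety question is left off by explicit design.

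Two stronger readings are tempting, and the article supports neither:

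- *Mail-only responders give no safety data.* This is too strong. Instructor reports, spontaneous reports and the person's other interviews remain. Only someone missed by telephone at every follow-up is never asked.
- *The people reached only by mail are those most likely to have been harmed, so event rates are biased downward.* This is plausible, but the article identifies the group only by not answering repeated calls and gives no reason for it. A bias figure would need event rates in telephone and mail responders, and the article gives neither.

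**Conclusion.** The point holds in a limited form. At any time point where a participant answers only by mail, that person is observed for efficacy and unasked about harms and serious health problems. Other channels may fill the gap in part. They do so least in usual care, after the classes end, and at week 52.

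The size is not known from the article. With 89% followed up and an assumed mail-only share of 0–15%, it is 0–40 people at a visit, and solicited safety coverage of 89% down to 76% of those randomized against 89% for outcomes. The gap in coverage does not depend on mail responders having more events than others, and no direction of bias is claimed. This is a minor point about safety ascertainment; it changes neither the sample size nor the efficacy analysis.

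**What to change.** Add to the mailed form, in the interview's wording, the brief item on new serious health problems (all arms) and the item on harm from classes or home practice (class arms only). Send any positive reply into the weekly adverse-experience review that the protocol already provides. At each time point, report the number asked about adverse experiences separately from the number with primary outcomes, by arm.

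The form already carries about 24 items (23 RDQ activities plus one rating), so this adds two at most. The cost is a slightly longer form and possibly a small loss in returns. If the sponsor considers even that too much, separate denominators alone require no change to data collection. Recruitment ended in April 2014 and follow-up runs 52 weeks, so any mailings still outstanding can use the longer form; for those already sent, only the reporting can be corrected.
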